### Sample size

2.8

According to the Cochrane review from Fransen et al. (2015), the average (between‐group) effect size (ES) of usual exercise therapy in knee OA on knee pain is 0.49, corresponding with a between‐group difference in mean improvement of 1.2 points (on 0–10 scale). In an RCT, comparable with our proposed study but in low back pain (Hill et al., 2011), stratified exercise therapy by a PT resulted in a (between‐group) ES of 0.3, compared with usual exercise therapy, corresponding with a between‐group difference in mean improvement of 0.5 points (on 0–10 scale). Based on a mean improvement 1.2 points (on 0–10 scale) for usual exercise therapy, our experimental intervention should result in a mean improvement of 1.7 points (on 0–10 scale). As this is lower than the mean improvement of 2.1 points found in our uncontrolled pilot study (*n* = 50; Knoop et al., 2019), this effect is highly plausible. With an expected between‐group difference in mean improvement of 0.5 points (on 0–10 scale), an estimated standard deviation of 1.4, α = .05 (two‐sided testing), power = 90%, design effect of 1.05 (with an estimated mean number of patients per cluster [i.e., PT practice] of 6), and 15% dropout rate, 408 patients (204 per group) will be needed.

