A pilot study (Knoop et al., 2019), testing this model of stratified care in the primary care setting (*n* = 50), provided promising results and thereby impetus for a fully powered trial. The pilot study demonstrated clinical improvements on knee pain (within‐group effect size of 1.1 and mean improvement of 37%) and physical function (0.7 and 20%). In addition, participating PTs provided on average less treatment sessions compared with usual care (10 vs. 17 sessions, Leemrijse et al., 2016). Finally, in interviews, PTs were positive about the applicability of the stratification tool (i.e., easy to use and not time‐consuming), and both patients (i.e., easy‐to‐perform exercises and tailored patient education) and PTs (i.e., subgroup‐specific treatment protocols) acknowledged the added value of the stratified care model. The pilot study also revealed some limitations in the model, and as such, we adapted our model to address this, prior to our planned trial. First, because one of the four subgroups (“depression subgroup”) had a very low prevalence, we decided to remove this subgroup from our model, which we discussed more in detail in our pilot study manuscript (Knoop et al., 2019). Second, clinical improvements in the obesity subgroup were lower compared with the other subgroups. Therefore, we decided to optimize our intervention of this subgroup by adding an obligatory weight‐loss intervention from a dietician, instead of only advising the patient to consult a dietician. This combined intervention of weight loss and exercise therapy can be expected to be more effective in this subgroup, based on recent evidence of superior effects in reducing clinical symptoms over weight loss only or exercise only in overweight and obese patients with knee OA (Messier et al., 2013). Third, we decided to reduce the cut‐off point for the obesity subgroup from BMI of 35 to 30, so every person with obesity (i.e., BMI ≥ 30) receives this combined, interdisciplinary intervention. Fourth and final, in our pilot study, knee extension strength was measured by a hand‐held dynamometer, which is a costly instrument demonstrating large variations. Therefore, we decided to replace this instrument into the 30‐s chair stand test, which is a reliable and easy‐to‐perform, functional test of lower body strength (Dobson et al., 2012).

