Our study design has several other strengths. First, this trial will be conducted in a primary care setting in “real‐world” patients in a large number of patients and PTs, so our findings can be expected to be representative for daily practice. Second, our intervention has already been found to be feasible in primary care with promising results on outcome measures but had been further improved on the basis of the study findings from our pilot study (Knoop et al., 2019). Therefore, it is unlikely that we will face feasibility issues during our trial. Third, our sample size has been calculated to detect minimal clinically important differences between groups and also enable us to perform explorative, secondary analyses to compare both interventions within each subgroup. Fourth, we added a dietary intervention to our subgroup‐specific exercise therapy intervention for the obesity subgroup. This interdisciplinary approach is not provided in usual care and can be expected to optimize current treatment effects in this complex and increasing patient group. Fifth, our outcome measures cover a broad spectrum of clinical and economic constructs, whereas we also collect detailed (quantitative and qualitative) information on treatment content, fidelity, and adherence. Thereby, the OCTOPuS study will gain new insights how to further optimize exercise therapy for patients with knee OA.

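### The SD of 1.4 is not reconciled with the effect sizes printed beside it, so the stated 90% power holds only if that SD does

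*Protocol article*

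**What the plan says.** Section 2.8 of the protocol article fixes the target as follows: "With an expected between‐group difference in mean improvement of 0.5 points (on 0–10 scale"). It combines this with "an estimated standard deviation of 1.4", "α = .05 (two‐sided testing), power = 90"%, a design effect of 1.05 and 15% dropout, and arrives at 204 patients per group.

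Three sources for the effect are quoted, each with both a standardised and a raw figure:

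- **Back-pain trial of stratified care (Section 2.8).** A between-group "ES of 0.3, compared with usual exercise therapy", which the text equates with 0.5 points. The 0.5-point target comes from here.
- **Knee OA review (Section 2.8).** The average between-group effect size of "usual exercise therapy in knee OA on knee pain is 0.49", equated with 1.2 points.
- **The pilot (Sections 1 and 2.8).** The Introduction gives a within-group "effect size of 1.1 and mean improvement of 37"%, and Section 2.8 gives the raw improvement as 2.1 points.

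Section 2.8 then takes 1.2 points as the improvement expected under usual exercise, adds 0.5 to reach 1.7, and defends that figure: "As this is lower than the mean improvement of 2.1 points found in our uncontrolled pilot study". Section 3 says that "our sample size has been calculated to detect minimal clinically important differences between groups". Section 2.9.1 allows adjustment for prognostic or imbalanced baseline characteristics, including the outcome measure, only where this is judged necessary.

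**The concern.** A raw difference divided by its effect size gives the SD that the effect size was standardised on. The plan takes 0.5 points from a source that calls this an effect size of 0.3, then divides by 1.4. That makes the same 0.5 points an effect size of 0.36. The other two pairs imply larger SDs still. The sample size therefore rests on a more favourable standardised effect than its source reports, and the text does not explain the change.

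What is at stake is how the result will be read. With 90% power on record, a null finding for pain would be taken as an adequately powered negative. If the true SD is nearer 1.9 or 2.4, that reading would not be justified. In the other direction, Section 3 invites a reader to treat a 0.5-point difference as clinically important, although Section 2.8 chose it because it was expected.

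**Working it through.** **Inputs.** Difference 0.5, SD 1.4, two-sided alpha 0.05 (z = 1.960), power 90% (z = 1.2816), design effect 1.05, dropout 15%, equal numbers of patients per arm. All are from Section 2.8.

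**Step 1: reproduce the plan.** n per group = 2 × (1.960 + 1.2816)² × (1.4/0.5)² = 164.8. Times 1.05 = 173.0. Divided by 0.85 = 203.5, so 204 per group and 408 in total. This matches the plan.

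**Step 2: implied SDs (points ÷ effect size), with the range that rounding of the printed figures allows.**

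- Back-pain trial: 0.5/0.3 = 1.67. Range 0.45/0.35 = 1.29 to 0.55/0.25 = 2.20, which includes 1.4.
- Pilot: 2.1/1.1 = 1.91. Range 2.05/1.15 = 1.78 to 2.15/1.05 = 2.05, which excludes 1.4.
- Knee OA review: 1.2/0.49 = 2.45. Range 1.15/0.495 = 2.32 to 1.25/0.485 = 2.58, which excludes 1.4.

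**Step 3: power of 408 patients for 0.5 points.** Effective n per group = 204 × 0.85/1.05 = 165.1. Power = Φ(0.5/(SD × √(2/165.1)) − 1.960). The detectable difference at 90% power is 3.2416 × SD × √(2/165.1). The last column repeats Step 1 with each SD.

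| SD | Source | Power for 0.5 | Detectable at 90% | Total N for 90% |
|---|---|---|---|---|
| 1.40 | Section 2.8 | 90% | 0.50 | 408 |
| 1.67 | back-pain trial | 78% | 0.59 | 578 |
| 1.91 | pilot | 66% | 0.68 | 758 |
| 2.45 | knee OA review | 46% | 0.87 | 1246 |

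Using the t distribution changes these powers by less than half a percentage point. At the most favourable rounding, the pilot SD of 1.78 gives 72% and the review SD of 2.32 gives about 50%. The back-pain source with exactly 0.5 points and an effect size of 0.35 gives SD 1.43 and 89%.

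**Step 4: could 1.4 be a reduced SD?**

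- As a residual SD after baseline adjustment, 1.4 = SD × √(1 − r²). The baseline-to-follow-up correlation r must be about 0.54, 0.68 or 0.82, starting from 1.67, 1.91 or 2.45.
- As a change-score SD with equal variances, 1.4² = 2 × SD² × (1 − r). This needs r of about 0.65, 0.73 or 0.84.

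The article states no correlation. For illustration, assuming r = 0.5, baseline adjustment would reduce the three SDs to 1.44, 1.65 and 2.12, with power of about 88%, 78% and 57%.

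**Step 5: the plausibility argument.** The 1.2 points enters as a between-group difference. The Introduction gives the corresponding effect size (rounded to 0.5) against no treatment and reports within-group improvement separately, as percentages. Section 2.8 then uses 1.2 as the improvement within a usual-exercise arm. The resulting 1.7 is compared with 2.1, an uncontrolled within-group change. A between-group quantity has been carried into a within-group comparison, so the inequality does not support the 0.5-point assumption.

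**The case against.** The strongest defence has four parts.

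- **The calculation is correct, and the source of the target is compatible with it.** A reader might infer an arithmetic error, or that 1.4 lies below every SD the article implies. Neither is supported. The 408 reproduces, and rounding lets the back-pain figures reach 1.4. This part stands.
- **The other two SDs are indirect.** The pilot effect size is within-group and its standardiser is not stated. The review figure is an average across trials, and the SD behind it is not identified. Eligibility also limits baseline walking pain to at least 2 and below 9, which narrows the baseline spread. This stands as a caution against taking 1.91 or 2.45 as the SD of the analysis. It does not reconcile 1.4 with them.
- **The planned analysis is richer than a two-sample comparison.** It is a multilevel model over time-points and may include baseline covariates, so its residual SD could be 1.4. This stands in part. It shows how 1.4 could be right, but Section 2.9.1 does not commit to the adjustment that this reading needs.
- **An article leaves detail to the full protocol.** That is a fair answer to the lack of a citation for 1.4 and of a calculation for the second primary outcome, KOOS daily living. Neither is counted here. The point concerns printed figures that do not agree.

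It is also true that the plausibility argument and the Section 3 sentence do not enter the formula. Removing them leaves 408 unchanged.

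**Conclusion.** The point holds as an input conflict. Section 2.8 states 90% power without condition, but it depends on an SD of 1.4 that is not reconciled with the pilot and review figures and agrees with the back-pain figures only through rounding. If the printed pairs give the SD of an unadjusted analysis, power for 0.5 points is about 78%, 66% or 46%, and the difference detectable at 90% power is 0.59, 0.68 or 0.87 points.

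A reader might conclude that the trial's power simply is 46% to 78%. The documents do not support that. The range assumes that those SDs transfer to this trial, that no baseline adjustment is made, and that the design effect and dropout are as stated. What can be said is that the 90% is conditional, and that the article does not give the condition.

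The plausibility argument and the claim about clinical importance are secondary wording errors. The first mixes two kinds of change. The second is not what Section 2.8 does, since that section uses an expected difference.

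**What to change.** Keep 408 patients and make these changes:

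1. **Section 2.8.** Replace the unconditional 90% with power, or the detectable difference, over SD 1.4 to 2.45, naming the source of each value. State whether 1.4 is an end-score, change-score or baseline-adjusted SD. If it is adjusted, give the assumed baseline-to-follow-up correlation.
2. **Section 2.9.1.** Make adjustment for the baseline value of the outcome mandatory in the primary model. Table 2 shows that both primary outcomes are already measured at baseline. Record this before outcome data are analysed.
3. **Section 2.8, wording.** Delete the argument that runs from 1.2 through 1.7 to 2.1.
4. **Section 3, wording.** Delete the statement that the sample size targets clinically important differences.

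The cost is a text change and one covariate fixed in advance, with no further recruitment or data collection. The stated power becomes less favourable, while mandatory adjustment recovers some of it if baseline and follow-up pain are correlated.

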### Analysis

2.9

#### Effectiveness evaluation

2.9.1

All patients included in the study will be analysed, with missing data from withdrawals handled by maximum likelihood estimation (“dealing with missing values”). Statistical significance will be accepted at *p* values of less than .05 (two‐sided testing). Baseline patient and PT characteristics in both study groups will be presented using descriptive statistics (mean/standard deviation, median/range, or proportions) to check similarity between arms. Descriptive statistics comparing both study groups will also be calculated for other study parameters (e.g., costs and process parameters). The primary analysis will be an intention‐to‐treat, multilevel, regression analysis comparing stratified versus usual care for the primary outcome measures, with 3‐month follow‐up as a primary time‐point and 6‐ and 12‐month follow‐up as secondary time‐points. In this analysis, we will take into account the level of PT practice, level of patient, and level of time‐point. In addition, we will perform a post hoc analysis with an additional level of PT, with the appropriateness of this additional level tested using the −log 2 likelihood test. Furthermore, we will perform a post hoc analysis comparing stratified versus usual care but now separately for each of the three subgroups. Only if deemed necessary, the analysis should be adjusted for important prognostic characteristics that potentially confound the treatment effects (e.g., pain severity, duration of symptoms, upper leg muscle strength, and BMI) or for important baseline patient characteristics (e.g., outcome measure) or PT characteristics that substantially differ between the two arms. We will perform similar analyses for secondary outcomes measures, except for GPE, which is analysed as a dichotomous variable (“completely recovered” and “much recovered” vs. all other responses), using logistic multilevel analysis.

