**Figure 1 pri1819-fig-0001:**
[figure not shown]
Flow chart of participating physiotherapists (PTs) and patients in the OCTOPuS‐study

Eligible PT practices were randomly allocated to experimental or control group in a 1:2 ratio (i.e., around one third to the experimental group and two thirds to the control group, with each group including 204 patients). The rationale for this allocation ratio is that PTs in the control group will only need to include and treat half of the patients compared with PTs in the experimental group. Because PTs expressed interest in our study primarily because of the training on stratified exercise therapy, a low number of patients will enhance their motivation for this study and minimize the risk of withdrawal. The random allocation was performed separately for practices with 2–3 participating PTs (Stratum 1) and for practices with 4–5 participating PTs (Stratum 2), in order to minimize the risk of not having a 1:2 ratio of PTs allocated to the two treatment arms. Within each stratum, all PT practices were grouped into three, of which one was randomly allocated to the experimental arm and two to the control arm.

PTs allocated to the experimental group were trained to provide the experimental intervention (i.e., stratified exercise therapy; see Section 2.6). A 4‐hr training session was organized to train PTs to provide treatment according to the model of stratified exercise therapy (see Section 2.6), to perform screening, and to supervise physical tests. PTs in the experimental group additionally followed an e‐learning course on the most recent Dutch PT guideline on knee and hip OA, prior to the training session. PTs allocated to the control group were provided a 2‐hr training session to instruct them to provide usual care (see Section 2.6), to perform screening, and to supervise physical tests. The training session on the experimental intervention and the e‐learning course will also be provided to the PTs from the control group but after the study period.

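### Treatment effects are to be compared separately in three subgroups with no interaction named, and the sample size said to enable this gives about 47% to 48% power per subgroup if the subgroups are equal

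*Protocol article*

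**What the plan says.** Section 2.9.1 (Effectiveness evaluation) sets a general two-sided 5% significance rule and describes the primary multilevel analysis. It then adds what it calls a post hoc analysis, "comparing stratified versus usual care but now separately for each of the three subgroups". No term for arm by subgroup is mentioned.

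Section 2.8 (Sample size) is built on one contrast, the overall comparison of arms on knee pain. It uses a "difference in mean improvement of 0.5 points", "an estimated standard deviation of 1.4", 90% power and a "design effect of 1.05", and ends with "15% dropout rate, 408 patients (204 per group) will be needed". It makes no allowance for subgroups and gives no expected subgroup shares.

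The Discussion lists the sample size among the strengths of the design and says that it will "also enable us to perform explorative, secondary analyses to compare both interventions within each subgroup".

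**The concern.** Separate tests answer three questions of the form 'is there an effect here?'. They do not answer 'is the effect larger here than there?'. A significant result in one subgroup beside a non-significant one in another is not evidence that the two effects differ.

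This matters because the experimental arm is three different packages (Table 1): a few sessions centred on self-management, supervised strengthening, and adapted exercise with a dietician. Once the trial reports, readers will want to know which package works, and three p values set next to each other invite that comparison.

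The Discussion may also raise expectations that section 2.8 does not support. A trial sized for its overall contrast has far less information in a third of its patients, so a null result in one subgroup could easily be taken as evidence that its package does not work.

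A smaller point is the label. An analysis written down before the results is planned, so 'post hoc' misdescribes its standing.

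**Working it through.** **Inputs from section 2.8.** Difference 0.5; SD 1.4; two-sided α 0.05 (z = 1.96); power 90% (z = 1.28); design effect 1.05; dropout 15%; 204 patients per arm. Section 2.5 confirms that although practices are randomised 1:2, patients are split equally, "with each group including 204 patients".

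**Reproducing the stated figure.** n per arm = 2 × 1.4² × (1.96 + 1.28)² / 0.5² ≈ 164.8, rounded up to 165. Then 165 × 1.05 = 173.25, and 173.25 / 0.85 = 203.8, so 204 per arm and 408 in total. This matches exactly, so there is no hidden reserve for subgroups.

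**Power in an equal third (assumed share).** Evaluable patients per arm = 204 × 0.85 / 3 = 57.8.

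- Without a design effect: SE = 1.4 × √(2/57.8) = 0.260; power = Φ(0.5/0.260 − 1.96) = 48.4%.
- With design effect 1.05: effective n = 57.8/1.05 = 55.0; SE = 1.4 × √(2/55.0) = 0.267; power = Φ(0.5/0.267 − 1.96) = 46.6%.

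The stated 1.05 with 6 patients per practice implies an intracluster correlation of 0.05/5 = 0.01. A single subgroup has fewer patients per practice, about 2 if thirds, so its design effect is nearer 1.01. The two results above therefore bracket the plausible value.

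**Difference detectable at 90% power, equal thirds.** (1.96 + 1.28) × SE = 0.84 points with SE 0.260, and 0.87 points with SE 0.267, against the planned 0.5. At 80% power with design effect 1.05 it is about 0.75 points.

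**Other shares** (15% dropout, design effect 1.05, difference 0.5):

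| Share of patients | Evaluable per arm | Power |
|---|---|---|
| 20% | 34.7 | 31% |
| 25% | 43.4 | 37% |
| 30% | 52.0 | 43% |
| one third | 57.8 | 47% |
| 40% | 69.4 | 54% |
| 50% | 86.7 | 63% |

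**Share needed for 80% power.** n per arm = 2 × 1.4² × (1.96 + 0.84)² / 0.5² ≈ 123; 123 × 1.05 / (204 × 0.85) = 0.745, or about three quarters of all patients.

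**Chance of a mixed pattern when nothing differs.** Suppose that the effect is 0.5 points in each of three equal subgroups and treat the tests as independent. P(some significant, some not) = 1 − p³ − (1 − p)³. With p = 0.466 this is 1 − 0.101 − 0.153 = 0.746; with p = 0.484 it is 1 − 0.113 − 0.137 = 0.749. So about 75% either way.

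**What an interaction contrast could show.** For two equal-third subgroups whose effects differ by 0.5 points, the SE of the difference is 0.267 × √2 = 0.377, and power = Φ(0.5/0.377 − 1.96) ≈ 26%. The interaction test is the right test for the question, but it is also weak.

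**The case against.** The best defence is that the protocol never says it will test whether effects differ between subgroups. It says that it will compare the arms within each one. Since each subgroup receives its own package, that is a sensible target, and low power is normal in an analysis that the Discussion itself calls explorative and secondary. Multilevel regression also yields estimates with intervals, not only p values. This stands in part: the within-subgroup effects are worth reporting, and the fix keeps them. It does not remove the risk that three separate tests are read against each other, which the 75% figure describes.

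The analysis plan is not shown and could contain an interaction term without contradicting the article. That is fair. The point rests on the method that the article does state, not on a missing detail.

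A reader might draw stronger conclusions that the document does not support:

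- That power is 48% or less in every subgroup. Unless the shares are exactly equal, at least one subgroup exceeds a third and so exceeds that power. The bound is certain only for the smallest subgroup.
- That the article makes a false power claim. It quotes no subgroup power, and it attaches the word 'explorative' to the sentence in question.
- That a large, fixed number of subgroup tests is planned. The article does not say which outcomes or time-points the subgroup analysis covers.
- That control patients cannot be classified. BMI and the 30-s chair stand test are scheduled at baseline with no restriction by arm, and control therapists were trained to supervise the physical tests. How control patients are coded is detail that an article may leave to the fuller documents.

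**Conclusion.** The concern holds as a limitation of an exploratory analysis. The stated method is separate testing, which cannot show whether the effect differs between subgroups. The sentence saying that the sample size enables these comparisons has no support in section 2.8, which covers the overall contrast only.

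The 47% to 48% rests on equal thirds, the planned dropout, and the SD of 1.4 applying within each subgroup. The broader conclusion does not need equal thirds. The smallest subgroup can hold at most a third of patients, so at least one subgroup has power of about 48% or less. No more than one subgroup could hold the three quarters needed for 80%.

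Nothing here touches the primary analysis or the 408, which reproduces exactly. The change is worth making before unblinded results are seen, but the main result does not depend on it.

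**What to change.** 1. Replace the three separate comparisons with one multilevel model on all patients containing arm, subgroup and arm by subgroup, evaluated at 3 months. Report the interaction test and the three subgroup effects with confidence intervals from that model.
2. State that subgroup is derived in both arms by applying the same stratification algorithm (Figure 2) to baseline BMI and chair-stand score.
3. Call the analysis pre-specified exploratory instead of post hoc.
4. Qualify the Discussion sentence: say that the sample size was set for the overall contrast and that within-subgroup comparisons have low power.

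The cost is wording in the analysis plan and one sentence in the paper; the data are already being collected. The small downside is the weakness of the interaction test shown above. A non-significant interaction must not be read as proof of equal effects, and the subgroup result should be read as estimates with intervals.

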### Blinding

2.4

In order to avoid contamination, patients are blinded for treatment allocation, which is in line with current recommendations for pragmatic CRCTs (Weijer et al., 2011). This means that patients from each treatment arm are informed about their own intervention only, without providing information on the intervention from the other treatment arm. Due to the nature of the intervention, blinding of participating PTs or dieticians is not possible. However, PTs from the control group are not informed about the experimental intervention. All participating PTs and dieticians agreed with the instruction to provide treatment strictly according to the protocol (experimental group) or according to their usual care (control group).

Blinding of the researchers (main researcher and research assistant(s), who are responsible for study coordination, contact with eligible candidates, participants, PTs, and dieticians, and data collection [all questionnaires and t12 physical tests], data monitoring, and data analysis) is not possible, as they need information about treatment allocation for adequate study coordination. However, a researcher blinded for treatment allocation performed the randomization of PT practices and will prepare the dataset and primary statistical analyses. For randomization, we used a web‐based randomization program, with concealment of randomization guaranteed.

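### Adjustment of the primary analysis, even for the baseline value of the outcome, is left to a judgement made after the arms are compared, with no criterion

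*Protocol article*

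**What the plan says.** Section 2.9.1 (Effectiveness evaluation) sets the primary analysis as an intention-to-treat multilevel regression with levels for practice, patient and time-point. It names no covariate that is always in the model. The rule for covariates reads "Only if deemed necessary, the analysis should be adjusted for important prognostic characteristics that potentially confound the treatment effects", with pain severity, symptom duration, muscle strength and BMI as examples. The same sentence extends the condition to baseline patient characteristics, giving the outcome measure itself as the example, and to "PT characteristics that substantially differ between the two arms". It does not say what makes adjustment necessary, how large a difference is substantial, or who decides. The section also says that baseline data will be tabulated to check whether the arms are similar.

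Table 2 in Section 2.7 shows both primary outcomes measured at t0. Section 2.5 describes stratified randomisation by practice size: "The random allocation was performed separately for practices with" 2–3 participating therapists and for those with 4–5. Section 2.9.1 does not mention that stratum.

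**The concern.** A covariate earns its place in the primary model by how strongly it predicts the outcome, which can be judged before any data are seen. It does not earn it by how far the arms happen to differ. A rule triggered by observed difference leaves the baseline score out when the arms look balanced, although a correlated baseline improves precision then as well. A rule triggered by perceived necessity, with an open list of candidates, allows more than one primary result from the same data, and the article does not say which one counts.

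At stake are which estimate is the trial's answer for pain and function at 3 months, and precision that could be had at no cost. The article states this rule itself, so it is not a detail left to an analysis plan. A plan that fixed the covariates would contradict the published text.

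**Working it through.** **1. The plan's own sample size.** Section 2.8 gives a "difference in mean improvement of 0.5 points (on 0–10 scale), an estimated standard deviation of 1.4", two-sided α 0.05, 90% power, a "design effect of 1.05" and 15% dropout.

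- Per arm: n = 2(1.960 + 1.282)² × 1.4² / 0.5² = 164.8, so 165.
- Clustering: 165 × 1.05 = 173.25.
- Dropout: 173.25 / 0.85 = 203.8, so 204 per arm and 408 in total.

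This matches exactly and uses no covariate adjustment. Working back, 204 × 0.85 / 1.05 is about 165 effective patients per arm, with power 90.1%.

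**2. What fixed baseline adjustment would add.** The article does not give the correlation r between baseline and 3 months; I assume 0.4 to 0.6. Nor does it say whether 1.4 is the SD of the follow-up score or of the change. Both readings are therefore shown, taking equal variances at the two times.

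- Against an unadjusted follow-up score: variance ratio 1 − r², residual SD 1.4√(1 − r²).
- Against a change score: σ²(1 − r²) / [2σ²(1 − r)] = (1 + r)/2, residual SD 1.4√((1 + r)/2).

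| r | Follow-up SD: variance cut | Power, same 408 | N for 90% | Change SD: variance cut | Power, same 408 | N for 90% |
|---|---|---|---|---|---|---|
| 0.4 | 16% | 94.3% | 344 | 30% | 97.3% | 288 |
| 0.5 | 25% | 96.3% | 308 | 25% | 96.3% | 308 |
| 0.6 | 36% | 98.2% | 262 | 20% | 95.2% | 328 |

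Check at r = 0.5: SD = 1.4 × √0.75 = 1.212; standard error = 1.212 × √(2/165) = 0.133; 0.5/0.133 − 1.96 = 1.79, which gives 96.3%. The two readings agree at 0.5 and move in opposite directions away from it.

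**3. Type I error under different uses of the rule.** The simulation used 20,000 null trials, 165 patients per arm, r = 0.5, one covariate and no clustering. The Monte Carlo standard error near 5% is √(0.05 × 0.95 / 20,000) = 0.15 percentage points.

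| Way of choosing the model | Two-sided type I error |
|---|---|
| Unadjusted, fixed in advance | 5.0% |
| Adjusted, fixed in advance | 5.0% |
| Adjust only if baseline difference has p < 0.05 | 4.4% |
| Adjust only if baseline difference exceeds 0.2 SD | 4.3% |
| Smaller of the two p values | 7.5% |

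The imbalance rules are conservative because the unadjusted test is kept when the arms are balanced, and its standard error is then larger than it need be. Only deliberate choice of the better result pushes the error above 5%.

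**The case against.** **Power.** A reader might infer that the trial is underpowered. The documents do not support that: 408 follows from the stated inputs with no adjustment, so what is lost is extra precision. One mixed case would do worse. If 1.4 were the SD of change but raw 3-month scores were analysed, power would be 94.5%, 90.1% and 82.7% at r = 0.4, 0.5 and 0.6. Nothing in the article establishes that combination, so it is no part of the finding.

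**Type I error.** A reader might also infer that the written rule inflates false positives. Its stated triggers are confounding and observed difference, not a favourable result, and a mechanical version is slightly conservative. The 7.5% describes misuse. What stands is that the article fixes no mechanical rule, so the discretion is real.

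**Precision.** Time-point is a level of the model and t0 is measured. If t0 enters as a repeated outcome with a mean common to both arms, most of the gain is already obtained. This is fair, but the article does not say so, and making baseline adjustment conditional gives no sign of it.

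**Stratum.** An article may leave this term to the full plan. Section 2.5 gives its purpose as keeping the 1:2 ratio of therapists, no figure shows practice size to be prognostic, and omission tends to be conservative. It is a minor addition and does not carry the point.

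**Recruitment.** Therapists who know their allocation recruit the patients, so imbalance may be genuine confounding. That is a reason to name prognostic covariates beforehand, not to choose them on sight.

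**Blinding.** Section 2.4 says "a researcher blinded for treatment allocation performed the randomization of PT practices and will prepare the dataset and primary statistical analyses". That lessens the risk of a choice guided by results but supplies no threshold, and the imbalance rule still requires the arms to be compared. Whether the blinding would hold is a separate question resting on inference, and the point does not depend on it.

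**Conclusion.** The concern holds as a badly fixed rule. The primary result depends on an undefined judgement made after the arms are compared, and the baseline outcome, normally the strongest candidate covariate, is optional.

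The forgone precision is 16–36% of the variance against a follow-up score, or 30–20% against a change score, for r from 0.4 to 0.6. At r = 0.5 that is 25%, which means about 96% power instead of 90%, or 308 patients instead of 408 for the same power. These figures rest on an assumed correlation, equal variances, the design effect and dropout in Section 2.8, and a baseline not already used as a repeated outcome.

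Type I error lies between about 4.3% (mechanical rule) and 7.5% (worst case of choosing between two models at r = 0.5, clustering ignored). The documents support neither a shortfall against 90% power nor an inflated error rate under the rule as written.

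**What to change.** Replace the conditional sentence in Section 2.9.1 with:

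> The primary model includes the baseline value of the outcome and the randomisation stratum (2–3 vs 4–5 PTs) as fixed covariates regardless of observed imbalance. Any other prognostic covariates are named before outcome data are seen by arm. Adjustment prompted by observed imbalance is a labelled sensitivity analysis.

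If t0 is instead to be modelled as a repeated outcome with a common baseline mean, say so; that can serve in place of the baseline covariate. The baseline outcome is the essential term and the stratum a minor one. Other terms, such as BMI or the chair stand score, are optional provided they are named in advance.

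The cost is wording only. Both primary outcomes are already measured at t0, the stratum is known from randomisation, and neither the sample size nor data collection changes.
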